**Fig. 1 Fig1:**
[figure not shown]
Schedule of follow-up activities. UV, unscheduled visit ; PK, pharmacokinetics ; AL, artemether-lumefantrine ; Pf, Plasmodium falciparum. ^1^ if screening parasitemia performed more than 2 h before h0. ^2^ first and last PK sampling times randomly allocated (first: h6 or h12 or h24 or h36 or h48; last: day 14 or day 21). ^3^ In case of treatment failure, additional capillary sampling for PCR genotyping and concentration of lumefantrine. ^4^ Hemoglobin concentration assessed at any point during follow-up if deemed necessary according to clinical condition. ^5^ Restricted to patients enrolled in Mali

#### Pharmacokinetics

Lumefantrine concentrations will be analysed using a population-based approach to restrict the number of samples required per child [29]. To achieve adequate precision in the estimation of PK parameters, assays will be conducted in 150 SAM and 150 non-SAM children. SAM children participating in the PK analysis will be the first consecutive patients recruited in both study sites, and non-SAM will be those recruited just after each SAM case.

For ethical and practical reasons, wherever possible, we will combine the PK samplings with other samplings performed for assessing parasitological efficacy. PK modelers have the following population sampling scheme: The first collection will be performed at h6, h12, h24, h36 or h48 (time randomly allocated), the second at h60 (the evening of day 2), the third at h72 (just before the discharge), the fourth at day 7, and the fifth at day 14 or day 21 (randomly allocated). An additional dosage will be made on the day of failure, if parasitological failure occurs.

The random allocation sequence of PK sampling times will be computer-generated by Excel before the study starts. The randomization list with be retained in each study site by the investigators, who will directly implement the allocation sequence (no blinding is required).

The PK of artemether and its active metabolite, dihydroartemisinin, will not be performed due to the heavy burden in this vulnerable population as well as logistical concerns as three venous blood samplings between h0 and h8 then plasma storage and shipment at -80 °C would be required. As an alternative, the parasite clearance will be determined in all patients, as it is considered the best indicator of impaired efficacy of the artemisinin component of an ACT [30]. A prolonged parasite clearance in children with SAM would support an impaired efficacy of artemether, one possible cause being inadequate exposure to artemisinins. On the other hand, an unaltered clearance would suggest that artemisinin exposure and efficacy is adequate. The Data Safety Monitoring Board (DSMB) will have the responsibility to monitor closely parasite clearance data, and to recommend a protocol amendment adding artemether PK assessment if deemed necessary.

### Laboratory methods

During this study, only capillary blood from finger pricks will be collected. The total amount of blood required for each patient included will approximate 7 ml for the total duration of follow-up.

For malaria screening, the SD Bioline® HRP2 RDT (Gyeonggi-do, Republic of Korea*)* will be used.

Thick and thin blood films will be read using a 100x objective. A sample will be considered negative only after 200 microscopic fields have been evaluated. The number of *P. falciparum* asexual forms on the thick film will be counted using the technique recommended by the WHO against at least 200 leukocytes [31]. Parasite density will be calculated based on a hypothetical leukocyte density of 8000 leukocytes/μL. The presence of gametocytes will also be assessed. For internal quality control during the study, a blinded second evaluation of the slides will be conducted by a second microscopist and in case of important deviation between the two readings, the procedures will be revised. An external quality control will be carried out by an external laboratory periodically during the study, for a random sample of 10 % of the positive and negative films.

Hemoglobin concentration will be determined with a HemoCue B®-Hemoglobin brand device (Ängelholm, Sweden) on day 0 and day 28.

PCR genotyping of malaria parasites will be performed to differentiate between a recrudescence and a re-infection. For this purpose, samples will be collected at enrolment and at treatment failure (if any) on filter paper and stored individually in re-sealable, zippered pouches containing a desiccant and sheltered from moisture, excessive heat and light. PCR genotyping will be carried out at the MRTC laboratory in Bamako. PCR adjustment consists of comparing primary infection parasites with those responsible for secondary infections. Identical genotypes at the *glurp*, *msp-2* and *msp-1* loci are a sign of treatment failure, while distinct genetic profiles indicate reinfection [32]. The paired pre- (day 0) and post-treatment (day X) samples with similar genotypes will be classified as a recrudescence (true failures), while pairs with different genotypes will be classified as re-infections. This analysis will also allow the complexity of infection (single or multiple) to be determined.

For lumefantrine concentration assessment, capillary blood will be collected in a microcapillary tube coated with lithium heparinate, then immediately transferred to a filter paper previously treated by the laboratory of Cape Town (50 microliter of whole blood per spot). Once dry, the filter papers will be stored away from heat and excessive light and regularly sent to the Division of Clinical Pharmacology, University of Cape Town for analysis. Quality controls spiked by the analytical laboratory, specifically designed to control for the environmental conditions at the site and during storage, will be stored and sent under the same conditions. PK assays will be performed using liquid chromatography and tandem mass spectrometry (LC MS/MS).

At h0, for children enrolled in Mali, 3 drops of capillary blood will be placed on filter paper for the dosage of anti-AMA1 specific antimalarial antibodies by Elisa method. Analysis will be performed by MRTC, Bamako.

### Outcome measures

The primary outcome of this study is the proportion of patients having an adequate clinical and parasitological response (ACPR) as defined by the WHO [14] on day 28, after PCR correction. This proportion will be compared between SAM and non-SAM children. Kaplan-Meier analysis will be used to account for censored data.

Secondary outcomes are:Regarding treatment efficacy○ Corrected ACPR proportion on day 42○ Failure proportion by type (ETF, LCF, LPF) by day 28 and 42, as defined by WHO [14]○ Proportion of reinfection and recrudescence○ Time to parasite clearance and parasite clearance half-lifeRegarding PK of lumefantrine○ Area under curve (AUC) and other PK parameters (Cmax, Tmax, Clearance, Volume of Distribution)○ Concentration on day 7○ Concentration on day of failure (in case of failure)Regarding safety○ Type and frequency of adverse events

### Protocol deviations and withdrawals

Children will be followed until day 42 whenever possible. However, some reasons may lead to the interruption of monitoring (such as protocol deviation, study withdrawal, detection of a malaria infection with species other than *P. falciparum*, death, severe adverse event, loss to-follow-up…). In all cases, the date and reasons for the interruption will be collected in the report form.

### Adverse events

Safety and tolerability of AL have been previously assessed and the treatment has been recommended for routine clinical use. The summary of product characteristics of study drugs will be available to clinicians to help the assessment of all adverse events and their relation with study drugs.

Any clinical or laboratory adverse event occurring during the 42-day follow-up after dosing will be described by the investigator in a specific section of the case report form. The following information will be collected: date of onset, nature, severity graded on a scale from 1 to 4 (minor, moderate, severe, and life-threatening), seriousness, relationship with AL, action(s) taken, date of resolution, outcome.

A physician investigator will be available on site 24h per day for the management of adverse events. In case of a SAE, as defined by ICH (ICH, CIOMS, European directive 2001/CE/21), a specific SAE declaration form will be filled in by the site principal investigator within 48 h and sent to the investigator coordinator in Epicentre, the Ethics Committees and the DSMB. They will recommend any action to be taken (including early termination of the study). In addition, ethics committees who reviewed and approved the protocol will also receive periodical reports of aggregated data on AEs, at regular intervals throughout the study.

### Statistical considerations

Study data will be double entered using REDCap electronic data capture tools hosted at Epicentre [33] then data management and analysis will be performed with STATA 12, StataCorp®, College Station, TX, according to written data entry procedures and data management plan.

A flowchart will present the following information: number of patients screened, number of patients infected with *P. falciparum* malaria, number of patients infected by other *Plasmodium* species, number of patients excluded (and reasons why they were not eligible), number of patients enrolled and analyzable in each group of SAM and non-SAM children.

For all enrolled children, baseline characteristics will be presented for each group (SAM versus non-SAM).

#### Antimalarial efficacy

Clinical and parasitological efficacy outcomes will be presented for SAM and non-SAM children: number of ETF, LCF, LPF, ACPR, re-infection, recrudescence, mixed infection, by day 28 and day 42.

Two methods will be used to estimate the therapeutic efficacy in each group:The Kaplan-Meier survival analysis will be used to calculate estimates of survival without subsequent infection in both intent-to-treat and per-protocol populations. This analysis will allow accounting for censored data [15, 34].Logistic regression analysis will be used to compare at day 28 (and then day 42) the proportion of ACPR in patients for which the endpoint has been determined, excluding those lost to follow-up or with missing endpoint.

After univariate analyses, multivariate analyses using survival models (time to recurrence) and logistic regression (proportion of ACPR) will be performed where the therapeutic success will be explained by the degree of malnutrition and other cofactors, including lumefantrine PK profile.

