## Abstract

**Background:**

Malnutrition and malaria frequently coexist in sub-Saharan African countries. Studies on efficacy of antimalarial treatments usually follow the WHO standardized protocol in which severely malnourished children are systematically excluded.

Few studies have assessed the efficacy of chloroquine, sulfadoxine-pyrimethamine and quinine in severe acute malnourished children. Overall, efficacy of these treatments appeared to be reduced, attributed to lower immunity and for some antimalarials altered pharmacokinetic profiles and lower drug concentrations. However, similar research on the efficacy and pharmacokinetic profiles of artemisinin-combination therapies (ACTs) and especially artemether-lumefantrine in malnourished children is currently lacking.

The main objective of this study is to assess whether artemether-lumefantrine is less efficacious in children suffering from severe acute malnutrition (SAM) compared to non-SAM children, and if so, to what extent this can be attributed to a sub-optimal pharmacokinetic profile.

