### Hypothesis and aims

The research question is: Is the current recommended dose of AL for the treatment of uncomplicated malaria less efficacious in the children with severe acute malnutrition (SAM children) compared to the non-SAM children and is PK in cause? We hypothesize that AL efficacy might be impaired in SAM children, due to altered lumefantrine PK profile in this population.

The study aims to assess whether the current treatment dose is adequate for SAM children. It is expected that results will inform further recommendations for malaria treatment in this important target population.

The primary objective of the study is to compare the rates of adequate clinical and parasitological response (ACPR), after PCR correction, between SAM and non-SAM children, during 28 days of follow-up.

The secondary objectives are:To compare the day 7 lumefantrine concentration and PK profile of lumefantrine between SAM and non-SAM children (The PK of artemether will not be assessed due to feasibility concerns)To assess the effect of malnutrition on i) therapeutic efficacy, ii) PK profile of lumefantrine, with adjustment for other cofactorsTo compare the time to parasite clearance between SAM and non-SAM childrenTo compare the rates of different types of failure (early treatment failure (ETF), late clinical failure (LCF), late parasitological failure (LPF)) between SAM and non-SAM children;To evaluate the relationship between treatment failure and the concentration of lumefantrine in the blood;To compare the rates of reinfection and recrudescence during a follow-up period of 42 days between SAM and non-SAM children; andTo compare the nature and frequency of adverse events between SAM and non-SAM children.

As an exploratory objective, we also propose to evaluate the effect of malnutrition on the acquisition of specific antimalarial immunity. Malnutrition is known to cause relative immunosuppression, but very few studies documented its effect on specific antimalarial antibodies. We will compare the level of anti-AMA-1 antibodies at baseline between SAM and non-SAM children, after adjustment for age.

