## Methods/design

### Study design and sample size

MAL-NUT is a non-randomized non-blinded comparative trial designed to compare the efficacy of AL and the lumefantrine pharmacokinetic profile in SAM versus non-SAM children. The two groups to be compared will not be randomly allocated since they include different populations of children. Similarly, blinding is not applicable.

Enrolled children will receive AL orally at the WHO-recommended weight-based dose over 3 days under directly observed treatment, and will be followed prospectively for 42 days according to the standardized WHO methods for surveillance of antimalarial drug efficacy in high transmission settings [15].

Follow-up will allow detecting early and late clinical or parasitological failure, with PCR genotyping to distinguish recrudescence from reinfection. The lumefantrine PK profile will be assessed using a population-based approach to restrict the number of samples required per child.

Sample size calculations were designed to detect a minimum crude difference in the proportion of adequate clinical and parasitological response (ACPR) between SAM and non-SAM children, with a ratio of 1/2 between the two groups (to ease the recruitment of SAM children). A total number of 540 children (180 SAM and 360 non-SAM) would allow to detect a minimum difference of 8 % in ACPR proportion (87 % in SAM versus 95 % in non-SAM children), with a statistical power of at least 80 % and a 2-sided significance level of 5 %, and 15 % expected missing endpoints. Two thirds of the children will be enrolled in Mali during the 2013 and 2014 malaria seasons, and one third will be enrolled in Niger during the 2014 malaria season.

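### The multivariable efficacy models adjust malnutrition for lumefantrine PK, its hypothesised mediator, and no confounder-adjusted model without PK is described

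*Protocol article*

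**What the plan says.** Under Statistical considerations, Antimalarial efficacy, the article describes its multivariable analyses once. Survival models (time to recurrence) and logistic regression (proportion with adequate clinical and parasitological response, ACPR) will be fitted "where the therapeutic success will be explained by the degree of malnutrition and other cofactors, including lumefantrine PK profile". One clause governs both model types. No adjusted model without PK is described.

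Elsewhere PK has a different role. Hypothesis and aims states: "We hypothesize that AL efficacy might be impaired in SAM children, due to altered lumefantrine PK profile in this population". The second secondary objective there treats efficacy and the lumefantrine PK profile as two separate outcomes of malnutrition, each to be adjusted for other cofactors. The Abstract asks whether efficacy is lower in SAM children, "and if so, to what extent this can be attributed to a sub-optimal pharmacokinetic profile".

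PK is not measured in everyone. Under Data collection, Pharmacokinetics, "assays will be conducted in 150 SAM and 150 non-SAM children". These are the first consecutive SAM children and the non-SAM child recruited just after each, so they are not a random sample. The sample size of 180 SAM and 360 non-SAM was set "with a ratio of 1/2 between the two groups".

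The primary analysis (Outcome measures) is a Kaplan-Meier comparison of PCR-corrected ACPR at day 28, without PK.

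**The concern.** The stated hypothesis is a chain: SAM lowers lumefantrine exposure, and low exposure causes failure. A variable in the middle of that chain is not an ordinary adjustment covariate. Holding it fixed removes from the malnutrition coefficient whatever part of the effect travels through it.

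Two questions then share one model. The second secondary objective needs the total effect of malnutrition, adjusted for baseline differences between the groups. The attribution question in the Abstract needs the malnutrition effect with and without PK, in the same children. The model as worded supplies only the with-PK half of the second question.

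This matters because Study design and sample size says that the groups are not randomised and come from different populations. The Relevance section gives an example of the risk: in an earlier comparison of SAM and non-SAM children that found no loss of efficacy, the SAM children had lower baseline parasitaemia. A crude comparison cannot deal with that kind of imbalance. If the PK-adjusted coefficient were read as the adjusted malnutrition effect, a trial in which the PK hypothesis is true could be reported as showing little independent effect of SAM.

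**Working it through.** **Inputs from the article** (Study design and sample size; Pharmacokinetics): 180 SAM and 360 non-SAM; ACPR "87 % in SAM versus 95 % in non-SAM children", so failure is 13% v 5%; two-sided 5% level; 15% missing endpoints; PK in 150 + 150.

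**1. The article's own figure.** Evaluable children: 180 × 0.85 = 153 and 360 × 0.85 = 306, total 459. Power = Φ[(d − 1.96·SE0)/SE1], where SE0 uses the pooled proportion.
- Pooled ACPR = (153 × 0.87 + 306 × 0.95)/459 = 0.9233.
- SE0 = √[0.9233 × 0.0767 × (1/153 + 1/306)] = 0.0263.
- SE1 = √[0.1131/153 + 0.0475/306] = 0.0299.
- Power = Φ[(0.08 − 1.96 × 0.0263)/0.0299] = 82.9%.

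The stated minimum of 80% is reproduced (78.4% with a continuity correction). The crude odds ratio for failure is (0.13/0.87)/(0.05/0.95) = 2.84.

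**2. What a complete-case PK model would use.**
- Children without a PK profile: 540 − 300 = 240 (44%), made up of 30 SAM and 210 of 360 non-SAM (58%).
- Ratio: 1:2 becomes 1:1.
- Expected failures in all evaluable children: 153 × 0.13 + 306 × 0.05 = 35.2.
- Expected failures in the PK subset with the same 15% missing: 150 × 0.85 = 127.5 per group, and 127.5 × (0.13 + 0.05) = 23.0.
- Crude power for 87% v 95% in the subset, same formula: 67.9% with 150/150, 60.8% with 127.5/127.5.

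**3. Attenuation when PK enters the model.** This needs assumptions that the article does not give. Failure log-odds fall by 1 per SD of log exposure. The total effect is fixed at 87% v 95%. A share of the SAM effect passes through exposure. To reproduce 13% v 5%, the SAM effect at a given exposure plus the part passing through exposure must total 1.14 on the log-odds scale. The odds ratio expected with PK in the model is then exp[(1 − share) × 1.14], that is 3.13, 1.77 and 1.00 for shares of 0, 0.5 and 1. Logistic simulation with 1,500 replicates per scenario, no other covariates and 128 + 128 children in the PK subset gave:

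| Share through PK | SAM shift in log exposure (SD) | OR, no PK, all 459 (power) | OR, no PK, subset (power) | OR, PK in model, subset (chance p<0.05) |
|---|---|---|---|---|
| 0% | 0 | 2.88 (83%) | 2.90 (62%) | 3.16 (64%) |
| 50% | 0.57 | 2.82 (84%) | 2.88 (57%) | 1.76 (17%) |
| 100% | 1.14 | 2.86 (84%) | 2.93 (62%) | 1.03 (4%) |

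The total effect is the same in every row. Only the PK-adjusted column moves, and it moves towards 1 as the trial's own hypothesis becomes more true. In the first row the odds ratio rises from 2.90 to 3.16 although nothing is mediated. That is non-collapsibility of the odds ratio, and it matters when the two fits are compared.

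**The case against.** The primary result does not depend on this model. The Kaplan-Meier comparison and the univariate analyses report the crude total effect in all evaluable children, whatever the later models show. A reader might infer that the plan could erase the effect the trial is looking for. The documents do not support that: only the adjusted effect, a secondary objective, is at risk. This part of the objection stands.

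A model holding both malnutrition and PK is also legitimate. The Abstract asks how far PK explains a loss of efficacy, and the article separately plans to compare PK between groups and to relate concentration to failure. This stands too: the model should be kept and relabelled. What is missing is its companion without PK.

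The article condenses a fuller protocol, and an analysis plan may exist. Cofactor lists and the handling of absent PK are commonly left to such documents, and the wording could be read as a list of candidate covariates. A reader might infer that 240 of 540 children will be dropped, but that requires every multivariable model to contain PK and to be fitted to complete cases, and the article does not say so. The objection does not remove the point itself. The published sentence names PK as a cofactor of malnutrition in both model types, which conflicts with the hypothesis and with the second secondary objective.

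**Conclusion.** The point holds for the multivariable efficacy models. As worded, their malnutrition coefficient excludes the PK-mediated part of the effect, and no confounder-adjusted total effect is described for a non-randomised comparison.

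Its size depends on the share mediated, which is unknown. Under the assumed exposure slope, the PK-adjusted odds ratio ranges from about 3.2 (none) through 1.8 (half) to 1.0 (all), against about 2.8 to 2.9 without PK. A reader might infer that the adjusted effect will vanish if the hypothesis is right. That follows only under full mediation. The Abstract also attributes the reduced efficacy of earlier drugs to lower immunity and asks to what extent PK is responsible, so partial mediation is contemplated. The survival models were not simulated.

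The upper limit of 300 children and the fall from about 35 to 23 expected failures assume complete-case fitting and the same 15% missing in the PK subset. The primary analysis, the sample size and data collection are unaffected.

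**What to change.** Replace the single description with two labelled analyses.

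(a) **Adjusted effect of malnutrition.** Malnutrition plus baseline confounders (such as age, parasite density, and site/season), without PK, in all evaluable children. Name this as the estimate for the efficacy part of the second secondary objective.

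(b) **Attribution to PK, exploratory.** In the PK children only, fit the same model without and with lumefantrine exposure and report the change in the malnutrition effect as a direct-effect analysis. Give standardised risks beside the odds ratios, because an odds ratio can change when a prognostic covariate is added even with no mediation. State that about 23 failures allow only low precision and that the PK children are not a random sample of the trial.

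If day-7 concentration is the exposure, state that children who fail before day 7 cannot contribute to (b), so early treatment failures, which count against ACPR, fall outside it. The day-of-failure concentration cannot stand in, because it exists only for children who fail.

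If the full protocol or analysis plan already separates these models, a sentence saying so is enough. Otherwise the cost is wording and extra model fits, with no new data.
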